# WOmen's Action for Mums and Bubs (WOMB) Trial Protocol: A Non-randomized Stepped Wedge Implementation Trial of Participatory Women's Groups to Improve the Health of Aboriginal and Torres Strait Islander Mothers and Children in Australia

**DOI:** 10.3389/fpubh.2020.00073

**Published:** 2020-03-18

**Keywords:** indigenous health, complex intervention, cluster stepped wedge, community participation, maternal and child health, empowerment

## Abstract

**Introduction:** In Australia, there have been improvements in Aboriginal and Torres Strait Islander maternal health, however inequities remain. There is increasing international evidence illustrating the effectiveness of Participatory Women's Groups (PWGs) in improving Maternal and Child Health (MCH) outcomes. Using a non-randomized, cluster stepped-wedge implementation of a complex intervention with mixed methods evaluation, this study aims to test the effectiveness of PWGs in improving MCH within Indigenous primary care settings in Australia and how they operate in various contexts.

**Methods:** This study takes place in ten primary health care services across Australia and involves the recruitment of existing PWGs or the setting up of new PWGs. Services are paired based on geography for practical reasons and two services commence the PWG intervention at three monthly intervals, with the initial four services being those with existing women's groups. Implementation of the PWGs as an intervention involves training local facilitators of PWG groups, supported engagement with local MCH data through workshops, PWGs identifying and prioritizing issues and strengths and co-implementing solutions with health services. Outcomes are measured with yearly MCH audits, a cost-effectiveness study, and process evaluation of community participation and empowerment.

**Discussion:** This study is the first to formally implement and quantitatively, yet with contextual awareness, measure the effect of applying a community participation intervention to improve the quality of Aboriginal and Torres Strait Islander MCH in Australia. Findings from this work, including detailed theory-producing qualitative analysis, will produce new knowledge of how to facilitate improved quality of MCH care in Indigenous PHC settings and how to best engage community in driving health care improvements.

**Trial registration:** Australian New Zealand Clinical Trials Registry (ANZCTR): ACTRN12618000945224.

Web address: http://www.ANZCTR.org.au/ACTRN12618000945224.aspx

## Introduction

The health, social and economic outcomes for Aboriginal and Torres Strait Islander Australians continue to be substantially worse than for other Australians (1–3). In Australia, improving the quality and consistency of PHC provided to Aboriginal peoples and Torres Strait Islanders is an essential part of the Australian Government's Close the Gap program (4). Maternal and child health (MCH) is consistently named a priority area by Aboriginal and Torres Strait Islander peoples, policy makers health service providers, and researchers (5, 6). Although Aboriginal and Torres Strait Islander infant mortality rates and the proportion of low birth weight babies born are falling, they remain almost double those of non-Indigenous infants (1).

Internationally, primary health care (PHC) is recognized as critical to addressing inequities in health status (2, 3). While Indigenous PHC services [both Aboriginal Community Controlled Health Services (ACCHS) and government services] provide PHC for Indigenous people, the quality of care and health outcomes can vary significantly between services (3, 7).

Continuous Quality Improvement (CQI) aims to facilitate ongoing improvement in the quality of PHC by using objective information to analyze and improve systems, processes and outcomes (8). A CQI strategy based on audit and feedback cycles of “plan, do, study, act” provides a theoretical, coherent and practical way for PHC services to identify, address and overcome barriers to quality care (9, 10). Modern CQI approaches incorporating service user participation, engagement, shared-decision making and tailoring to context address both scientific and humanistic values (10). Such approaches may also offer the potential to enhance MCH through the improvements in quality made in the PHC setting. International empirical evidence suggests that an integrated approach that includes community women as active participants (11) working alongside service providers can improve both the quality and outcomes of MCH care in a relatively short time period (11–13). Furthermore, CQI fits with the principles and values of Aboriginal and Torres Strait Islander people (expressed in national statements on research and cultural respect) (14, 15). Despite the demonstrated benefits of community participation (16), very few quality improvement interventions in Aboriginal and Torres Strait Islander PHC have focused on factors beyond service provision as part of their implementation. None have explicitly tested community participation aimed at enhancing community decision-making and co-production in health care and health service design. Similarly, in evaluating quality improvement interventions, the cost effectiveness of community participation in light of MCH improvements in service provision and health outcomes has not been assessed. Hence, there is a need to add to the evidence in this area.

There is persuasive international research illustrating the effectiveness of participatory women's groups (PWGs) in improving MCH outcomes such as neonatal and maternal mortality rates via improved quality of care, women's empowerment, and new learning (11, 16–18). There is considerable evidence internationally (19, 20) and in Australian Aboriginal and Torres Strait Islander settings (21) that empowerment of women is achieved through participation in such women's groups. Empowerment means healing from past wounds, developing strength and skills to live life in a positive way, to have good relationships with others and to work together to make communities a better place (22). A systematic review with meta-synthesis found that participatory interventions using women's groups are effective in improving neonatal and maternal survival (23). This led to the identification of PWGs, coupled with health systems strengthening and community action, as highly effective strategies for improving MCH that are low-cost, sustainable, and scalable.

Morrison et al. (20) have named four mechanisms to explain the positive impact of women's groups on health outcomes in a study of maternal and newborn health in Nepal. The groups: (a) learn about health; (b) develop confidence; (c) disseminate information in their communities; and (d) build community capacity for action (20). Based on this evidence, we hypothesize that improvements in MCH related to participation in PWGs may be mediated through measurable changes in empowerment.

The study discussed above took place in Nepal, with contextual factors including a weak health system funded through significant contributions from external development partners who are influential in decision-making. In addition, similar to most low-resource settings, the PHC system is dependent on extensive contributions from female community health volunteers (over 50,000 in Nepal). External agents call on these women volunteers to assist in conducting MCH interventions (24). By comparison, the Australian public health system is relatively strong and does not rely on volunteers to provide PHC services. Interventions are usually provided by health professionals, many of whom are unfamiliar with working collaboratively with women's groups. Yet, we know that working partnerships in Indigenous health are fundamental (25); PHC staff and managers need to be supported to understand the importance of community participation in co-producing responsive MCH services that aim to improve patient outcomes.

There are compelling examples of Aboriginal and Torres Strait Islander community responses to health and well-being needs that arise spontaneously within communities. The overarching example is the Aboriginal community controlled health movement as the expression of Indigenous cultural values within a predominantly western health sector (26). On a smaller scale, the Strong Women, Strong Babies, Strong Culture program in the Northern Territories employed older community women to work individually with pregnant women to improve health behavior and health care access. A small, but significant increase in birthweight over an 8 year period was demonstrated through this program (27). The Aboriginal-developed Family Wellbeing Program (FWB) is another empowerment-based participatory approach, designed to support the capacity for individuals, organizations and communities to gain control over their lives to improve wellbeing and quality of life (21, 28–30). FWB has been successfully applied by our team to MCH care, organizational change and team strengthening (amongst others). Reported benefits of FWB include greater understanding and mutual respect between health staff, an enhanced capacity to work with others toward common goals, and improved access to health services and high quality service delivery (31, 32).

This study examines whether PWGs, as an intervention, improve the quality of Indigenous MCH care. More specifically, it will determine the effectiveness of PWGs in improving quality of care and intermediate health and well-being outcomes in MCH; the cost-effectiveness of PWGs for improving quality of MCH care; the degree to which the PWGs are associated with a change in empowerment measured using the global empowerment measure (GEM) scores for women involved (22); and the processes through which PWGs exert effects in various contexts.

## Research Question and Objectives

Do participatory women's groups (PWGs), as an intervention, improve the quality of maternal and child health (MCH) care in Australian Indigenous primary health care (PHC) services?

The objectives are to determine:

The effectiveness of PWGs in improving quality of care and intermediate outcomes in MCH;The cost-effectiveness of PWGs for improving quality of MCH care;The degree to which the PWGs are associated with a change in global empowerment measure (GEM) scores for participating women; andHow and why PWGs exert their effects in various contexts.

## Methods and Analysis

### Design

A stepped wedge cluster implementation (non-randomized) of a complex intervention was chosen for ethical and logistical reasons. It allows all participating PHC services to receive the PWG intervention in sequential order, where evidence of effectiveness can be assessed with pre- and post-intervention observations from each service (33). This design has an advantage in improving power with smaller numbers of services where intra-cluster correlation is high (optimizing feasibility). By allowing services to act as their own historical controls it also accounts for underlying differences between clusters that may confound results in the more traditional parallel cluster designs. Through the collection of routinely recorded MCH audit data, the study assesses the effectiveness of a complex intervention involving PWGs addressing issues in MCH care to improve outcomes amongst Indigenous mothers and babies. To complement the design, qualitative research with PHC services and PWGs will explore contextual barriers and enablers to successful implementation of the PWG in various settings throughout Australia.

Recognizing that patients, clinicians and policy makers need real world evidence to make informed decisions about their healthcare, the study represents a range of typical Indigenous PHC settings, using realistically attainable intervention approaches under real-world conditions, and reporting relevant outcomes to all stakeholders (34).

To test the effectiveness of the PWG intervention, this design is blended with our commitment to a participatory approach informed by Indigenous ways of being, knowing and doing and an all-teach and all-learn philosophy. This is done in part through optimizing the flexibility to respond to the rich and varying needs and contexts of individual health services and communities, whilst maintaining the integrity and consistency of the intervention. One example of this is that initial meetings with participating services determined that there are two groups of services, four services with existing functional women's groups and active auditing (early services) and six services who do not yet have a functional women's group and/or have auditing delays (later services). Recognition of these differences, and a rejection of the concept of randomization as disempowering by participating services and partners has led to a revision of the design in terms of randomization of the order of intervention, as described below. Furthermore, service representatives and PWG facilitators are all involved in collaborative planning and training meetings, steering group meetings, and team communication strategies throughout the life of the study. This study protocol was developed as required by the Standard Protocol Items: Recommendations for Interventional Trials (SPIRIT) (Supplementary Material 1).

### Study Setting

This study is conducted in partnership with ten *primarily Indigenous* PHC services in Queensland, New South Wales, Northern Territory and Western Australia. *Primarily Indigenous* refers to services that are an Aboriginal Community Controlled Health Service or government service funded primarily to service Aboriginal or Torres Strait Islander people. Participating services represent a range of jurisdictions, service size, remoteness, governance models and CQI tools.

### Study Participants

The target population to whom our findings apply is primarily Indigenous PHC services and women and children who access Indigenous PHC services. Thus, PHC services are eligible to participate if they fulfil the following inclusion criteria: (a) are a primarily Indigenous PHC service (b) are engaged in some auditing of MCH service provision using a recognized and evidence-based audit tool (35, 36); (c) have a formal or informal community women's group associated with the service or a desire to establish one; (d) are willing to support at least one staff member to attend facilitator training; and (e) have agreement from CEO, Chair and key clinical staff to participate and share aggregated service level data during the study.

### The PWG Complex Intervention

PWG facilitators are recruited via the PHC service. The PHC services nominate two women leaders, ideally Aboriginal or Torres Strait Islander, to work as PWG facilitators. It is important to have at least two PWG facilitators trained in order to provide support and improve sustainability of the local PWG (for example, should one facilitator resign their position, or leave the area).

PWG membership eligibility extends to all female community members who have an interest in MCH and may include but is not limited to the following:

Pregnant womenMothersWomen who may be pregnant but not yet awareElders who are not health professionals.

An existing or new community women's health and wellbeing group forms the foundation of the complex intervention. Establishment of a new PWG or refreshing the membership of an existing group (if needed) will be led by the PHC service and may involve community consultation, engaging with existing community groups and other community organizations. PWG facilitators attend a training program during the set-up phase of the study. The purpose of this training is to build relationships and communication strategies between PWG facilitators and investigators; to share learning about facilitating the PWG; to become familiar with MCH audit data; and engage in a cyclical process of planning and implementation of changes to improve MCH called the Remote Service Futures (RSF) framework.

The RSF framework guides the PWG intervention planning and implementation process (37). The RSF uses a semi-structured approach to identifying needs, planning interventions, and implementation by community people in partnership with health professionals with monitoring via a series of workshops (38). This approach has recently been tested in Australian rural communities in improving oral health care, and found to be feasible when used with skilled facilitation (38–40). Table 1 outlines the RSF framework activities important in the PWG intervention.

**Table 1 T1:** RSF framework activities important in PWG intervention.

**Phase 1: Planning workshops**	**Phase 2: Implementation workshops**
Identification of PWG members	Workshop 1: Monitoring implementation of planned MCH improvements
Workshop 1: Sharing knowledge: What are some things that PWG members know about that affect the health of mums and bubs? What are the strengths and limitations of the maternal and child health (MCH) support services for this community?	Workshop 2: monitoring implementation of planned change
Workshop 2: Sharing knowledge of what is happening in the care and health of mothers and babies in the community—through national and local data, health service information, and other information regarding social issues (family support, access to adequate child care or housing, family issues).	Workshop 3: monitoring implementation of planned change
Workshop 3: Women share ideas on what might lead to MCH improvement. What can be done in the community to improve the health/care of Mums and Bubs? Share knowledge of what other Aboriginal and Torres Strait Islander communities have done in other relevant area.	Workshop 4: monitoring implementation of planned change
Workshop 4: Developing a community MCH improvement plan with prioritized items	Ongoing PWG activity as desired by community Ongoing implementation. Translation of outcomes

Following training, the facilitators return to their communities and consolidate or establish their PWG. The facilitators work collaboratively with PWG members on MCH improvements using the RSF framework. It is important for PWGs to link with existing community initiatives (for example, Health Action Teams, Domestic Violence support groups, breastfeeding peer-counselors). The role of women in these groups is to: share local knowledge and community perspectives, focus on building community expectations, encourage community ownership of services, engage in activism for high quality care, and plan and develop initiatives to improve MCH. MCH nursing and/or medical staff may also be included to build their own capacity to respond to community perspectives.

During the intervention, each PWG decides the exact timing and interval of the four planning workshops. These may be at approximately monthly intervals (completed in the first six months of the intervention, with the flexibility to accommodate significant community events). There is an ongoing relationship between the investigators and the PWGs so that technical support, for example, extra data, assistance in using audit data, or information about implementation of changes, can be provided if necessary. The type or frequency of technical support is recorded for each PWG and form part of the process evaluation of the PWG. PWG facilitators and members are informed that the MCH improvement plan needs to be cost neutral and within the remit of the health service and PWG/community to implement within a 12-month period. Three initiatives from the community MCH quality improvement plan will be prioritized for implementation, and these will be implemented and monitored through a series of four workshops over 8 months at intervals to suit the services (at approximately bimonthly intervals). Annual meetings will bring facilitators together to disseminate their experiences, share learning and enhance the knowledge base for groups to respond to local needs, issues and priorities. Strategies considered and implemented by groups will differ according to prioritized goals and what is contextually appropriate and might involve health service or community level initiatives. Examples from previous PWG interventions include patient-held records, service report cards, breastfeeding support groups and community education programs.

As part of the intervention, services are provided with AU$5,000 per year to support the study at their facility as they wish (for example, part compensation for staff time, producing health promotion resources in response to PWG group input). In addition, PWG facilitators receive a small amount of reimbursement (0.1Full Time Equivalent) during the intervention period to directly off-set time and contributions to the facilitation of the PWGs. Both of these are factored into the cost effectiveness analysis.

### Outcomes

The primary outcome measure is a change in the MCH Quality of Care Index (QCI) from aggregated de-identified health service audit data. The MCH QCI provides an indicator for overall adherence to delivering recommended services based on evidence based clinical best practice guidelines in the delivery of care. The MCH-QCI (%) is calculated from audit data as (total number of services provided)/(total number of recommended services) ^*^100 (Table 2) (41). Baseline audit data is collected from services at yearly intervals (over ~1 week at the end of each year) for the 5-year duration of the study. Given the stepped wedge start-time of the intervention, each service will have at least one set of pre-intervention audit data (some up to three) and at least two sets of post-intervention audit data (some up to four; Figure 1). Patients attending the services whose charts may be audited are women with an infant aged between 2 and 14 months at the time of audit, resident in the community for at least 6 months of the pregnancy and using the PHC service as her usual source of care.

**Table 2 T2:** Indicators included in MCH quality of care index.

Maternal Health QCI30 Clinical Indicators	Laboratory investigations: urinalysis (three time points), blood group, antibodies, full blood examination, rubella, Hepatitis B, syphilis serology, HIV, morphology US Physical examination: weight (two time points), body mass index; blood pressure (three time points); fundal height (two time points), fetal heart rate (two time points) History of risk factors: cigarette use, alcohol use, illicit drug use (each at two time points) Antenatal discussions: antenatal education, healthy living (nutrition, exercise, oral health, breastfeeding), psychosocial situation (domestic environment, family support, financial and housing)

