### Participant Timeline

The non-randomized cluster stepped-wedge design involves staged implementation of the intervention with two services commencing the intervention planning period at three monthly intervals (Figure 1). Initially, the study was planned to be randomized in terms of the timing of commencement of the intervention, but it became apparent that some of the services were ready much earlier than their allotted start date, based on the pre-existence of a functional women's group. We considered stratified randomization, but ultimately came to the conclusion (with our service partners) that imposing a randomized order on a complex intervention with a presumed theoretical basis of empowerment was likely to be counterproductive in terms of relationship building/engagement with community members and was unpopular with staff at participating services. Thus, randomization of start order was abandoned, and time of commencement will be adjusted for statistically as part of the analysis.

The first phase of the study is the start-up phase and involves study set up, engagement of stakeholders, recruitment of services, recruitment of PWG facilitators, training and formation of PWGs. At the first service engagement meeting in late 2018, services were paired in terms of timing of the intervention for practical reasons based on geographic proximity, to improve feasibility of support (both from the project team and from facilitators at the partner site). The four “early ready” services will embark on the complex intervention first, at three month intervals. The remaining six services have agreed an order of implementation based on perceived readiness (Figure 1). On commencing the intervention, there is a 6-month intervention planning phase comprising the RSF Phase 1 planning workshops and between two and three years for the implementation of MCH improvement plans and monitoring implementation of planned changes (RSF Phase 2) depending on the time of entry.

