### Sample Size

The study is conducted with ten services that have self-nominated and been engaged with MCH audits. The number of maternal records examined in a service at a single audit cycle ranges from <5 to >100, but is usually ~20. Actual mean of the MCH-QCI from 43 services previously involved with One21seventy MCH audits is 65.97% with standard deviation (SD) of 13.58% and a change of 5% is likely to be clinically significant. A stepped-wedge design with five steps, ten clusters and intracluster co-efficient of 0.15 and an average cluster size of 20 has a design effect of 0.40 (with only two baseline and one subsequent audit) (44). Using our expected sample size of 200 audit records from 10 services and a design effect of 0.4 with alpha = 0.05, an SD of 13.58, 99% power is achieved for detecting a 5% change in our primary outcome. This is a conservative estimate. This sample size also gives a statistically significant result if mean birthweight is 100 g higher after the intervention than in the pre-intervention state (e.g., 3.3 kg v 3.2 kg). For the proportion of pregnant women with their first antenatal visit prior to 13 weeks gestation, this study will produce a statistically significant result if the odds of a pregnant woman attending in the first trimester are 1.5 times higher in the PWG group than in the pre-intervention group.

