### Allocation

Two health services each commence the intervention at 3-monthly steps, and as discussed above, randomizing the order of intervention implementation was abandoned for ethical and theoretical reasons. This is now a non-randomized trial, still with a stepped wedge design and cluster intervention. Although not universally accepted, there are precedents for this design in the literature (45) including suggestions for analysis to compensate for the lack of randomization (46). The team's belief is that in a design with three month steps, and an expected time frame of 12 months for maximal effect the detrimental effects of this in terms of potential allocation bias are likely to be outweighed by relational benefits in terms of control and implementation. Services act as their own controls, thus no blinding at service level is either feasible or necessary. Analysis adjusts for the time of commencement of the intervention.

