### Data Collection, Management and Analysis

#### Primary and Secondary Outcomes

Cross-sectional data for the primary and secondary outcome measures are collected from services by service staff using the One21Seventy MCH audit tool (35) (from which the MCH-QCI can be obtained) based on evidence-based best practice guidelines about quality MCH care. Processes for conducting these audits and ensuring data quality are well described (3, 7, 41, 47). The MCH-QCI is calculated at the beginning of the study and on an annual basis using existing mechanisms and supports that are part of the inclusion criteria. At least five sets of audit data will be available for each service. This is adequate time to demonstrate significant impacts on quality of care and possibly some health outcomes such as birthweight. Patients attending the services whose charts may be audited are women with an infant aged between 2 and 14 months, resident in the community for at least 6 months of the pregnancy and using the PHC service as her usual source of care.

Data, from which the primary and secondary outcome measures (MCH-QCI) will be drawn, is the property of the PHC service and the service forwards de-identified data to the research team for analysis. This data is in electronic form using a template designed by the research team. This template includes the name and a full description of the variable. Members of the investigator team including the statistician are responsible for checking the templates sent by PHC services and responding to any data queries.

The unit of analysis for the primary outcome is the health service. For the primary analyses (for both primary and secondary outcomes), it is likely that the PWG will have an effect on outcomes after 12 months from the start of the intervention at each step. The outcomes will be analyzed using linear mixed effects models. The models will have a random effect for community, and fixed effects for the effects of time. Estimates of the effect of PWGs will be reported along with 95% confidence intervals. Secondary analyses may adjust for rurality, service size, number of audit cycles and governance structure (ACCHS or government service), and various sensitivity analyses may be undertaken. Statistical significance is set at *p* < 0.05 level to test the hypothesis that there was a significant change in each of the outcome measures from baseline score. Imputation analysis is used to account for the effect of missing data.

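### The stated one to three audits before and two to four after the start do not fit five starts three months apart with one audit a year

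*Protocol article*

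**What the plan says.** All references are to the protocol article.

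- **Outcomes.** Audit data are "collected from services at yearly intervals (over ~1 week at the end of each year) for the 5-year duration of the study". Each service is said to have "at least one set of pre-intervention audit data (some up to three") and at least two post-intervention sets, with some having up to four. Figure 1 is cited for this and is not available in the text reviewed.
- **Participant Timeline.** The roll-out has "two services commencing the intervention planning period at three monthly intervals". Each service has a 6-month planning phase and then two to three years of implementation, depending on when it enters.
- **Allocation.** The spacing is repeated: "Two health services each commence the intervention at 3-monthly steps".
- **Sample Size.** A design with "five steps, ten clusters and intracluster co-efficient of 0.15 and an average cluster size of 20 has a design effect of 0.40", the last figure resting on two baseline audits and one subsequent audit.
- **Primary and Secondary Outcomes (data collection).** "At least five sets of audit data will be available for each service", and the index is calculated at the start of the study and then annually.
- **Design.** The case for the design without randomised order includes that differences between services are handled "By allowing services to act as their own historical controls".

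**The concern.** The number of audits before and after each start defines the contrast from which the effect is estimated. Because the order of starts is not randomised, the trial leans on each service's own before-period. It also leans on services crossing over at different audit rounds, since that is what separates the intervention effect from calendar time. The Outcomes section describes services crossing over at three different points in the audit sequence. If the roll-out and audit calendar allow only two, the protocol states a property that its own schedule does not deliver. Either the longest before-period or the longest after-period is then overstated. The sample size calculation, which assumes that services are separated at five steps, may also not describe the data that will be collected.

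**Working it through.** **Inputs.** Five steps, ten services, 20 records per audit, ICC 0.15, SD 13.58, target change 5 points, alpha 0.05 (Sample Size; two-sided assumed). Starts every 3 months (Participant Timeline, Allocation). One audit per year end for 5 years (Outcomes).

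**Step 1: roll-out length.** Five starts have four gaps: 4 × 3 = 12 months.

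**Step 2: spread in before-audits.** Let the first start be at month F and the last at F + 12. The difference in before-audits between the last and first pair is the number of year-end audits after F and up to F + 12. Audits are 12 months apart, so that number is one. A spread of two needs the starts to straddle two consecutive year ends, which takes more than 12 months.

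**Step 3: enumeration.** Audits are at months 12, 24, 36, 48 and 60. An audit that coincides with a start counts as before.

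| First start (month) | Before | After | Part of the Outcomes range not reached |
|---|---|---|---|
| 12 to <24 | 1–2 | 3–4 | up to three before |
| 24 to <36 | 2–3 | 2–3 | up to four after |

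Earlier first starts leave some services with no before-audit. Later ones leave some with fewer than two after. Counting after-audits only from 6 or 12 months past the start, or adding a sixth audit at month 0, still leaves services differing by one round. Starts 4 months apart (a 16-month span) could produce one to three.

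**Step 4: which row is likelier.** Assume that implementation ends with the fifth audit at month 60. Three years of implementation after 6 months of planning means a start at 60 − 36 − 6 = month 18. Two years means 60 − 24 − 6 = month 30. That span is again 12 months, in agreement with Step 1. Starts at months 18, 21, 24, 27 and 30 give 1, 1, 2, 2 and 2 before-audits and 4, 4, 3, 3 and 3 after.

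**Step 5: the plan's design effect and power.** The stepped-wedge design effect with k = 5 steps, b = 2 baseline audits, t = 1 audit after each step, n = 20 and ICC ρ = 0.15 is

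[1 + ρ(ktn + bn − 1)] / [1 + ρ(ktn/2 + bn − 1)] × 3(1 − ρ) / [2t(k − 1/k)] = (21.85 / 14.35) × 0.2656 = 0.404,

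which reproduces 0.40. Dividing 200 records by 0.40 gives 500, so SE = 13.58 × √(4/500) = 1.215 and power = Φ(5/1.215 − 1.96) = 98.4%, close to the stated 99%. This formula implies b + kt = 2 + 5 = 7 audit rounds, with a pair crossing over before each of the last five.

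**Step 6: illustrative power for the yearly schedule.** Generalised least squares on service-by-audit means, with fixed audit-round effects and a random service intercept. Between-service variance is 0.15 × 13.58² = 27.66. The variance of an audit mean around its service is 0.85 × 13.58² / 20 = 7.84. Power = Φ(5/SE − 1.96).

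| Schedule | SE | Power |
|---|---|---|
| 7 rounds, one pair per round | 1.22 | 98% |
| 5 audits, services split 4/6 or 6/4 between two crossover points | 2.01 | 70% |
| 5 audits, split 2/8 or 8/2 | 2.46 | 53% |
| 5 audits, assumed 4/4/2 split over 1, 2 and 3 before-audits | 1.63 | 86% |

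The two five-audit splits give the same SE in either row of the Step 3 table. Two further before-audits for every service move the 53% to 70% range only to about 55% to 73%.

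**The case against.** The Outcomes wording gives bounds, not an attained range. If the calculation at the beginning of the study is a sixth audit, 2–3 before and 3–4 after satisfies every phrase read loosely. That is fair, although the stated minimums would then describe no service. The conflict is also close to a boundary: a slip of days or weeks around two consecutive year ends would produce a spread of two. Figure 1, which may carry the dated schedule, is not available. These points limit the finding to the schedule as written in the text.

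Three stronger readings are tempting, and the document does not support them.

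- **That the before-period is necessarily shorter than claimed.** Under the second row of the Step 3 table three before-audits do occur, and the after-count is the one overstated. The 12-month lag expected before an effect also means that an audit soon after a start may still reflect care before any effect.
- **That a chance low or high baseline biases the effect through regression to the mean.** That would need starts to be ordered by audit score. Participant Timeline describes ordering by readiness, existing groups and geography.
- **That one audit's standard error is too large for the target.** A single service's audit mean has a standard error of 13.58 × √(0.85/20) = 2.80 points. The 5-point target is for an effect pooled over ten services in a mixed model, so the two are not comparable.

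**Conclusion.** The inconsistency stands. A spread of two audit rounds between services conflicts with a 12-month roll-out and one audit per year end, which allow a spread of one. With five audits, either the upper figure for before-audits or the upper figure for after-audits cannot be reached. On the assumption that implementation ends with the fifth audit, it is probably the before-count, with 1–2 audits per service and none with three. This rests on the three-monthly spacing being kept and on year-end audits happening on time.

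The design effect and power reproduce within rounding, but for a schedule of seven rounds with five crossover points. The 53% to 70% is illustrative: it assumes an immediate, constant effect, variance components known at the stated values, and no extra audit-to-audit variation within services. It shows that the audit schedule matters for the power claim, and it is not a definitive power for the trial.

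**What to change.** 1. Add a dated table of audit rounds by service with each start marked, and correct the counts in Outcomes to match it. Reconcile it with Participant Timeline, the statement on numbers of audits under data collection, and Figure 1, and say whether the start-of-study calculation is an extra round.
2. Check the design effect in Sample Size against that table. If there are not two baseline audits and one after each of five separate steps, recalculate and restate the power.
3. Where services hold earlier audits with comparable items and agree to share them, include these as pre-intervention data and use them to examine each service's trend before its start. This is plausible because eligibility requires some existing auditing, and the first to start are "four services with existing functional women's groups and active auditing (early services").

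Items 1 and 2 cost a table, a corrected sentence and a recalculation. Item 3 needs further agreement, since the services own the data and the agreement in the inclusion criteria covers sharing during the study. Gaps are likely in services with auditing delays, and items whose definition has changed would have to be left out. The gain is mainly in checking prior trends, with little added precision.
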